### IRT measurement

#### Measuring locations

The skin temperature of 11 acupoints most commonly used for KOA will be measured [12]. The most commonly used acupoints include *dubi* (ST35), *neixiyan* (EX-LE5), *xiyangguan* (GB33), *yanglingquan* (GB34), *heding* (EX-LE2), *liangqiu* (ST34), *zusanli* (ST36), *xuanzhong* (GB39), *weizhong* (BL40), *yinlingquan* (SP9), and *xuehai* (SP10). The positioning of acupoints is shown in Table 1, which follows WHO Standard Acupuncture Locations.

**Table 1 pone.0284381.t001:** Positioning of acupoints.

Acupoint	Location
*Dubi* (ST35)	On the anterior aspect of the knee, in the depression lateral to the patellar ligament
*Neixiyan* (EX-LE5)	On the anterior aspect of the knee, in the depression medial to the patellar ligament
*Xiyangguan* (GB33)	On the lateral aspect of the knee, in the depression between the biceps femoris tendon and the iliotibial band, posterior and proximal to the lateral epicondyle of the femur
*Yanglingquan* (GB34)	On the fibular aspect of the leg, in the depression anterior and distal to the head of the fibula
*Heding* (EX-LE2)	On the anterior aspect of the thigh, in the depression superior to the base of the patella
*Liangqiu* (ST34)	On the anterolateral aspect of the thigh, between the vastus lateralis muscle and the lateral border of the rectus femoris tendon, 2 cun ^a^ superior to the base of the patella
*Zusanli* (ST36)	3 cun directly below ST35, and one finger-breadth lateral to the anterior border of the tibia
*Xuanzhong* (GB39)	On the fibular aspect of the leg, anterior to the fibula, 3 cun proximal to the prominence of the lateral malleolus
*Weizhong* (BL40)	On the posterior aspect of the knee, at the midpoint of the popliteal crease
*Yinlingquan* (SP9)	On the tibial aspect of the leg, in the depression between the inferior border of the medial condyle of the tibia and the medial border of the tibia
*Xuehai* (SP10)	On the anteromedial aspect of the thigh, on the bulge of the vastus medialis muscle, 2 cun superior to the medial end of the base of the patella

^a^ 1 cun (≈20 mm) is defined as the width of the interphalangeal joint of patient’s thumb.

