### Sample size calculation

The relative skin temperatures of 11 acupoints are the primary outcomes of this study. The relative skin temperature of acupoints were preliminary extracted from the IRT images of 30 KOA patients and 30 healthy individuals at the clinic. The mean values of the KOA and healthy groups were 0.11°C and -0.23°C respectively, with the same standard deviation of 0.79°C in both groups. With 2-sided α = 0.0045 (adjusted for 11 primary outcomes using Bonferroni adjustment), 149 participants will be needed to provide 80% statistical power. Considering an attrition rate of 15%, a total of 340 participants (170 per group) are expected to be recruited.

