### Data correction and statistical analysis

#### Correction of skin temperature

Human skin temperature is individual and affected by basal body temperature [30]. A previous study [31] showed that relative temperature, which can control bias from individual differences, is more valuable than absolute temperature under specific conditions. Relative temperature can eliminate the systematic error caused by factors such as body and ambient temperature, and truly express the temperature characteristics in the ROI. Using the quantification method of relative temperature, the temperature value in the ROI will be subtracted from the temperature value of other regions (reference areas) specified in the same image. In this study, at the same time that the absolute temperature will be reported, relative temperature will be analyzed as the main indicator. The specific correction formula for relative temperature is as follows:

$$T_{c}=T-\bar{T}$$

*T_c_* is the measured value of the skin temperature of the acupoint after correction. *T* is the absolute skin temperature of the acupoint (the actual value measured). $\bar{T}$ is the control temperature, means the average skin temperature of the corresponding reference area. As shown in Fig 4, the reference area is the entire lower limb region on the IRT image which used to locate the acupoint.

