#### Statistical analysis

For this study, the statistical analysts will be blinded. SAS version 9.3 (SAS Institute, Cary, NC, USA) or R software will be used for statistical analysis. Measurement data will be described as the mean ± standard deviation (M±SD) or median and interquartile ranges, and counting data will be described as frequency, constituent ratio or percentage. Independent samples t-tests or χ2 tests will be used to test the equilibrium of demographic data with a significance level of 0.05. The intraclass correlation coefficient (ICC) will be used to obtain the test-retest reliability of the temperature extracted by different researchers. A two-way random model with absolute agreement will be used for ICC calculation. An ICC value greater than 0.75 for each relative skin temperature of the acupoints evaluated will be considered to have good reliability. Comparison of relative skin temperature and absolute skin temperature between groups will be performed by Z test or χ2 test. For the relative skin temperature of acupoints, P < 0.0045 will be considered statistically significant. For other measurements, P < 0.05 will be considered statistically significant. Missing values and extreme values in demographic data will be confirmed and modified by phone calls before analysis. Other missing data will be inputted by the mean/mode completer.

Exploratory analysis will include the exploration of correlations and contributory factors within relative skin temperature at different acupoints. To simplify the factor structure of multiple relative skin temperatures of acupoints, when Kaiser-Meyer-Olkin (KMO) measurement value is > = 0.5 and Bartlett’s sphericity test value is <0.05, exploratory factor analysis will be adopted. After clustering and dimensionality reduction of temperature in two groups, the common factors will be extracted by principal component analysis. Then, the Kaiser normalized maximum variance method will be used to calculate the factor loading and factor score coefficient matrix to obtain the score of each common factors and acupoints’ relative skin temperature. A general linear regression model will be used to explore the influence some factors on skin temperature of acupoints. In the model, dependent variable will be the comprehensive factor scores; fixed factors will include age, gender, BMI, pain site and NRS, among which age and BMI will be transformed into qualitative data.

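### Acupoints on one image share a subtracted limb mean, so the exploratory factors and the score regression can partly reflect the reference area or camera view

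*Protocol article*

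**What the plan says.** Under Correction of skin temperature, the protocol article defines the analysed value as T_c = T − T̄. T̄ "means the average skin temperature of the corresponding reference area", and "the reference area is the entire lower limb region on the IRT image which used to locate the acupoint". The aim is stated there: "Relative temperature can eliminate the systematic error caused by factors such as body and ambient temperature".

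Under Statistical analysis, the plan goes on: "Exploratory analysis will include the exploration of correlations and contributory factors within relative skin temperature at different acupoints". If KMO is at least 0.5 and Bartlett's test gives a value below 0.05, the relative temperatures go into an exploratory factor analysis with principal component extraction and varimax rotation. A general linear model follows, in which the "dependent variable will be the comprehensive factor scores" and the explanatory terms are gender, pain site, NRS, and categorised age and BMI. It is the only model in the article that contains the terms of the secondary objective (gender, painful area, pain level).

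**The concern.** Points located on the same image all have the same number subtracted. If the rest of the limb on that image is unusually warm or cool, every one of those points moves together in the opposite direction, whatever happens at the points themselves. Points on another image have a different number subtracted. The text does not give the number of images, and the figures are not shown. Table 1 does place points on several aspects of the limb; BL40, for example, is "On the posterior aspect of the knee, at the midpoint of the popliteal crease".

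The plan then interprets how these values correlate and group. A shared subtracted term is a source of correlation, and KMO and Bartlett's test respond to correlation of any origin. A reported group of acupoints could therefore mirror a camera view. A reported influence of gender, pain site or NRS could also arise in the thigh, calf or foot.

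**Working it through.** **The plan's own figure.** The only figure that can be recomputed is the sample size, and this point does not depend on it. With a difference of 0.11 − (−0.23) = 0.34 °C, SD 0.79, two-sided α = 0.0045 and 80% power, the normal formula gives 147 per group. The t version gives 148.4, hence 149, as stated.

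**Model.** Inputs from the document: 11 acupoints ("The relative skin temperatures of 11 acupoints are the primary outcomes of this study"), SD 0.79 °C ("with the same standard deviation of 0.79°C in both groups"), n = 340, and the KMO/Bartlett thresholds. Let T_j = G + e_j, where G is the person's body/room level, and let the reference mean be G + r. Then

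T_c,j = (G + e_j) − (G + r) = e_j − r.

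G cancels and r stays. For points sharing a reference, with independent e_j, the pairwise correlation is q = var(r)/var(T_c). The document gives no value for q, so a range is used.

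**Step 1: the KMO/Bartlett condition.** Independent acupoints, 300 runs per row. The four-view split of 6/3/1/1 points is an assumption. R² is between the first principal component and the reference (of the six-point view in the four-view case).

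| q | One reference: condition met | R² | Four references: condition met | R² |
|---|---|---|---|---|
| 0 | 1% | – | 2% | – |
| 0.02 | 9% | 0.10 | 1% | 0.03 |
| 0.05 | 81% | 0.34 | 21% | 0.15 |
| 0.10 | 100% | 0.54 | 94% | 0.35 |
| 0.20 | 100% | 0.73 | 100% | 0.58 |
| 0.30 | 100% | 0.82 | 100% | 0.71 |

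**Step 2: view-shaped factors.** Same split, two factors with varimax, n = 340. The solution reproduced the two multi-point views in about 6% of runs at q = 0.05, about 60% at 0.10 and 100% at 0.20. At n = 170 it did so in 24% and 92% of runs at 0.10 and 0.20. On absolute temperatures such false view clusters appeared in 0–1% of runs. A real cluster crossing views was recovered there in 88–98% of runs when two factors were retained.

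**Step 3: dilution by real correlation.** Add a true knee factor shared by all points, with one common reference. If the knee factor takes 30% of var(T_c), the reference explains 12%, 22% and 47% of the first component at q = 0.05, 0.10 and 0.30. If it takes 10% and q = 0.30, the reference explains 66%.

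**Step 4: the regression.** A covariate's effect on T_c equals its effect on T minus its effect on T̄, with no assumption about q. Averaging points reduces the noise in e_j but not r. As an illustration, assume q = 0.2, one reference for all 11 points, equal weights, and a 0.2 °C gender difference in the reference only among 170 patients split equally:

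- Composite SD = 0.79 × √(0.2 + 0.8/11) = 0.413, so the difference is 0.2/0.413 = 0.48 SD.
- z = 0.485/(2/√170) = 3.16, giving P < 0.05 about 88% of the time. At a single acupoint the figure is about 38%.

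**Step 5: can the reference mean settle the source?** Compare (a) a shift of +δ in r alone with (b) a shift of +δ in G and a real acupoint effect of −δ in e_j. In both cases T changes by 0, T̄ by +δ and T_c by −δ. In simulation the rejection rates agreed: about 89% for relative values, 23–24% for the reference and 5% for absolute values under either mechanism. An opposite shift in the reference mean therefore does not show that an acupoint effect is absent.

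**The case against.** A reader might infer that the subtraction necessarily creates the correlations, secures passage of the KMO/Bartlett condition and makes the composite mostly a measure of the reference area. The documents do not support that:

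- **Net effect.** Subtraction mainly removes shared variance. With an assumed SD(G) of 0.5–1.5 °C, absolute temperatures correlate at 0.30–0.84, against 0.05–0.30 for relative ones at q = 0.05–0.30.
- **The reference contains the points.** If the limb is modelled as independent patches including the 11 points, the induced correlation is negative (−0.09 with 12 patches, −0.006 with 200) and the condition is met in 0–4% of runs.
- **Biology.** Most of the points surround one knee, so real correlation is likely and could meet the condition by itself.
- **Purpose.** A contrast with the limb is the declared main indicator, and a covariate effect on it is a valid result about that contrast.
- **Absolute values are no clean substitute.** At q = 0.2 and SD(G) of 0.5–1.0 °C, G would make up about 85–96% of an equally weighted absolute composite. The plan subtracts this term deliberately.

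Most of this stands and limits the claim. The patch model is the weakest part. Eleven circles of radius 3 pixels cover about 11 × 28.3 = 311 pixels, or 0.4% of a 256 × 336 frame, whereas in the 12-patch case they make up 11/12 of the reference. The 200-patch case simply leaves the reference almost no variance of its own. That the net correlation falls does not help either, because the correlation that remains is what the plan interprets.

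**Conclusion.** The point holds in a conditional form. Acupoints located on one image share a subtracted limb mean, so the factors and comprehensive scores can partly reflect the reference area or camera view, and the KMO/Bartlett condition cannot separate this from biology.

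The size is unknown because the document gives neither the reference's share of variance nor the division of points among images. With independent acupoints and view-specific references, the effect is small at a share of about 2–5%. At 10–20% or more it is enough to meet the condition and produce view-shaped factors. A real knee factor dilutes it, and the reference then dominates only if its share exceeds that factor's. The 88% illustration also rests on an assumed 0.2 °C shift and one reference common to all points, which the image-specific definition does not establish.

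The consequence is confined to the exploratory analysis and the secondary objective. The 11 primary comparisons, their significance level and the sample size use no factor scores.

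**What to change.** - Keep the relative-temperature factor analysis as the main version and repeat it on the 11 absolute temperatures, which are already extracted as secondary outcomes. In that repeat, retain at least one factor beyond the general body/room factor; an eigenvalue-above-1 rule may keep only the general one. Report a set of acupoints as a cluster only if it appears in both versions.
- Fit the same covariate regression to the absolute temperatures and to each image's reference mean, and report these beside the relative result.
- Word any gender, pain-site or NRS effect as an effect on the acupoint-minus-limb contrast, unless it is also seen in the absolute acupoint temperatures. Do not dismiss an acupoint effect only because the reference mean shifts the opposite way (Step 5).

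The cost is analysis wording and a few extra model runs on data already collected. The small downside is a general body/room-temperature factor in the absolute version, which must be read as such.

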### Secondary objectives

The secondary objective of this study is to explore the influence of gender, painful area and pain level on the skin temperature of acupoints in KOA patients.

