### Inclusion criteria

The inclusion criteria for the KOA group are as follow: (1) meet the ACR clinical diagnostic criteria [25] of KOA; (2) aged 45–70 years old; (3) have unilateral/bilateral knee pain for more than 6 months; (4) have X-ray examination showed Kellgren-Lawrence grade [26] Ⅱ or higher within 6 months; (5) score 4 or high in numerical rating scale (NRS) during the past week for knee pain; (6) sign the informed consent.

The inclusion criteria for the healthy control group are as follow: (1) without knee pain in the past year; (2) aged 45–70 years old; (3) signed informed consent.

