### Other measurements

#### Demographic data

Demographic data included gender, age, ethnicity, education, height, weight, BMI, etc. These data will be collected from all participants.

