#### Disease-related data

Disease-related data included NRS [29], pain sites (front, back, outside or inside), duration of pain, pain descriptors (stabbing, bursting, sore, burning, etc.), pain activities (going upstairs, going downstairs, standing up, walking, etc.).

The primary outcomes included the relative skin temperature of 11 acupoints, and the secondary outcomes included the absolute skin temperature of 11 acupoints and other measurements.

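### The only model given for the secondary objective has factor scores as its outcome, so it yields no effect for any single acupoint; it also categorises age and BMI and does not name its sample

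*Protocol article*

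**What the plan says.** The Secondary objectives section sets the task: to "explore the influence of gender, painful area and pain level on the skin temperature of acupoints in KOA patients". The population is the KOA group and the quantity is temperature at acupoints.

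The Statistical analysis section offers one model with these factors, in its exploratory paragraph. The outcome is prepared first: "After clustering and dimensionality reduction of temperature in two groups, the common factors will be extracted by principal component analysis". After rotation, scores are obtained and regressed: "In the model, dependent variable will be the comprehensive factor scores; fixed factors will include age, gender, BMI, pain site and NRS". The same sentence of the plan then says how two of the five covariates are to be coded: "among which age and BMI will be transformed into qualitative data". No cut-points are given, no group term appears, and the participants entering the regression are not named.

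Three other places bear on the sample. Patients must "score 4 or high in numerical rating scale (NRS) during the past week for knee pain", whereas controls must be "without knee pain in the past year". The pain variables are listed as disease-related: "Disease-related data included NRS [29], pain sites (front, back, outside or inside", with no level for no pain. The statement "These data will be collected from all participants" is made of the demographic data only.

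**The concern.** The study is meant to tell acupoints apart. The Discussion says its results will show which acupoints have abnormal temperature in KOA and so help clinicians choose among them. For the secondary question, however, the model replaces the 11 acupoint temperatures with factor scores. A reader could learn that pain at the front of the knee goes with a higher score on some factor, but not that it goes with a warmer ST35 or EX-LE5. Pain site is itself local (front, back, outside, inside), and Table 1 places the acupoints on those different aspects. Summarising across acupoints can therefore hide the pattern being sought.

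Two smaller matters sit in the same sentence. Cutting age and BMI into categories discards information and may leave residual confounding. And because the sample is unstated and there is no group term, an analyst who fitted all 340 participants could mistake the case-control difference for an effect of pain level.

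**Working it through.** **1. Objective against model**

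| | Secondary objectives | Statistical analysis |
|---|---|---|
| Population | KOA patients | Not named; factor step refers to two groups |
| Outcome | Acupoint skin temperature | Factor scores |
| Factors | Gender, painful area, pain level | The same, plus age and BMI |

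The factors agree. The outcome does not, and this holds whichever participants are fitted. No arithmetic is needed for it.

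**2. Planning figures.** The plan gives no figure for this model, so its primary sample size is used to check the inputs. From Sample size calculation: means 0.11 and −0.23 °C (difference 0.34 °C), SD 0.79 °C, two-sided α 0.0045, power 80%. The normal formula gives 147 per group and the noncentral t calculation gives 149, which is the stated figure. The inputs are read correctly.

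**3. If controls entered with NRS 0 and no group term.** Assumptions not in the documents: patient NRS takes the values 4 to 8 equally often (mean 6, variance 2); the score behaves like one relative temperature; 170 per group; other covariates are left out; the true NRS slope within KOA is zero.
- Pooled variance of NRS = 0.5 × 2 + 0.25 × 6² = 10.
- Covariance with the outcome = 0.25 × 6 × 0.34 = 0.51.
- False slope = 0.51/10 = 0.051 °C per NRS point.
- Residual variance = 0.79² + 0.25 × 0.34² − 0.051² × 10 = 0.627.
- Standard error = √(0.627/(340 × 10)) = 0.0136.
- Ratio = 0.051/0.0136 ≈ 3.76. Chance of P < 0.05 ≈ Φ(3.76 − 1.96) ≈ 0.96.

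Simulation (3,000 runs) agrees:

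| Fit | Mean slope, true 0 | Rejected at 5% | Mean slope, true 0.10 |
|---|---|---|---|
| Both groups, controls NRS 0, no group term | 0.051 | 97% | 0.061 |
| KOA only | 0.000 | 4.9% | 0.099 |
| Both groups with group term | 0.000 | 4.7% | 0.099 |

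The result hardly depends on the assumed NRS range. The same formulas with NRS 4 to 6 (mean 5, variance 0.67) give a pooled variance of 6.58, a slope of 0.425/6.58 = 0.065 and about 97% rejection. With NRS 4 to 10 (mean 7, variance 4) they give 14.25, 0.595/14.25 = 0.042 and about 96%.

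**4. Categorising age and BMI.** The share of linear information kept with k equal groups is the variance of the group means divided by the total variance. For two groups of a normal covariate this is 2/π = 0.637.

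| Groups | Normal covariate | Uniform covariate (1 − 1/k²) |
|---|---|---|
| 2 | 64% | 75% |
| 3 | 79% | 89% |
| 4 | 86% | 94% |

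Both shapes, and equal group sizes, are assumptions.

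**The case against.** The strongest reply is that the regression sample is clear in context. The objective is limited to KOA patients, and NRS and pain site are disease-related variables that pain-free controls do not have. A model with those factors and no group term is most naturally a KOA-only model. Mention of two groups in the factor step may also mean that each group is handled separately. This stands. A reader might infer that the model pools both groups and so cannot answer the question, or that half of its 340 records would lack a real pain value. The text does not say so, and a KOA-only fit would estimate gender, pain-site and NRS effects on the scores.

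A reader might also infer that the mean/mode rule would give controls invented pain values. That rule is for missing data, and a pain site that does not apply is not missing. Even taken literally, imputing the mean NRS left the slope unbiased in the simulation (0.000 and 0.099). A modal pain site given to controls would carry part of the group difference into the site effect, but only if two unstated readings both held.

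Nor can the dilution be given one figure. Suppose two of 11 points warm by 0.30 °C and all points are weighted equally. The average then moves 2/11 × 0.30 = 0.055 °C, 82% less in raw units. But the SD of an average also falls. The standardised effect goes from 0.30/0.79 = 0.38 to 0.055/(0.79/√11) = 0.23 if the points are independent, a loss of 40%. The loss reaches 82% only with perfect correlation. Effect, weights and correlations are all assumed, and varimax rotation may place neighbouring points on one factor.

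Finally, the analysis is exploratory, leaves the primary per-acupoint comparison untouched, and age and BMI are adjustment variables rather than the question. All true, and it limits the weight of the point. It does not remove the mismatch, since no other model is given for this objective.

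**Conclusion.** The concern holds in a limited form. On any reading, the stated model returns no effect of gender, pain site or pain level for an individual acupoint, and it can blur a local pain-site effect by an amount that the loadings will decide. If the factor step pools the groups, the case-control difference also helps to shape the outcome. Categorising age and BMI loses between 14% and 36% of their linear information for two to four equal groups of a normal covariate (6% to 25% if uniform), and may leave residual confounding. It does not stop the model from estimating the effects of interest.

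The unnamed sample is a risk rather than a demonstrated error. The natural KOA-only reading keeps the 5% error rate, while the pooled reading with controls at NRS 0 would give a false NRS effect in about 97% of runs. That figure rests on the planning difference of 0.34 °C, the planning SD and the assumed NRS range. The point is an inexpensive improvement to an exploratory analysis and does not affect the primary comparison.

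**What to change.** State that the secondary-objective model is fitted in KOA patients only. Use the relative temperature of each acupoint as outcome, either in 11 separate models or in one mixed model with acupoint-by-pain-site terms. Enter gender and pain site as categorical terms, and NRS, age and BMI as continuous terms. Keep the factor scores, derived within the KOA group, as a supplementary summary.

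This changes analysis wording only and needs no new data. The cost is more output and more tests, which should be reported as exploratory.

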Some sensitizations can be found on the body surface of KOA patients, such as pain sensitization and thermal alteration. These sensitizations can guide both diagnosis and treatment [14, 15]. Acupoints also have the characteristics of sensitization. The biological characteristics of acupoints (such as skin temperature [16], tenderness threshold [17], and morphology [18]) may change in pathological conditions. Acupoints are specific points on the body surface, and sensitizations of a certain area should be similar to those of acupoints within this area, which provides a basis for acupuncture therapy. As a typical example, acupoint selection of dry needling can be guided by trigger points [19]. However, these links to skin temperature have not been explored clearly. Most acupoint selection methods guided by sensitization phenomena have large individual differences, with difficulties expanding. As a little-attention part of sensitization, skin temperature may be a more universal and objective factor to guide acupoint selection.

Infrared thermography (IRT) is a technology that collects focal plane temperature information within the field of view and displays surface temperature distribution in pseudocolor form [20]. IRT has high temperature sensitivity, which can reflect blood circulation and metabolism of tissue to be applied in medicine as a diagnostic test or outcome measurement [21]. Some abnormal skin temperature areas can be found in patients with KOA or other osteoarthritis [22, 23]. Recent evidence suggests that thermal alteration can reflect the progress of KOA and guide medical practice [15]. However, there is insufficient evidence to link these sensitized areas to acupoints. To further understand the characteristics of acupoints under pathological conditions, this cross-sectional case-control study will explore special manifestations of skin temperature of acupoints in patients with KOA by IRT. The results of the study will provide a theoretical basis for further optimizing the selection of acupoints.

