To our knowledge, this is the first study to investigate the skin temperature of acupoints in KOA patients. IRT technology has the characteristics of noninvasive, nonradiation, noncontact and high repeatability. It is currently one of the best methods to measure the skin temperature of acupoints. For inflammatory diseases such as KOA, IRT can simply and clearly reflect the condition and guide medical treatment [15]. This will be a multicenter study in which patients will be recruited from primary and tertiary hospitals simultaneously. Patients included in this study will be a typical KOA population with any KL grade other than grade I, which is undiagnosable. Patients who underwent knee surgery or report NRS scores less than 4 will be excluded because we cannot ensure the stability of the lower extremity temperature in this population. Acupoints assessed will be the most common ones in clinical practice. Moreover, two temperature correction methods, an adequate sample size and a strictly corrected P value increase the credibility of this study.

This study still has a few limitations. First, the location of the ROI drawn by different researchers may be slightly different since the positioning of acupoints are rough positions rather than precise points. However, ROIs will be drawn repeatedly by different researchers to ensure the consistency of acupoint location. Second, this study only focused on skin temperature at acupoints, which is of limited reference value to therapies other than acupuncture.

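### The exploratory model for pain level and painful area leaves out Kellgren-Lawrence grade, so its NRS and pain-site effects may partly reflect disease stage, to an unknown extent

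*Protocol article*

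**What the plan says.** All places are in the protocol article.

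- **Secondary objectives:** the aim is to "explore the influence of gender, painful area and pain level on the skin temperature of acupoints in KOA patients".
- **Statistical analysis (exploratory part):** a general linear model is named. Its "dependent variable will be the comprehensive factor scores", and its "fixed factors will include age, gender, BMI, pain site and NRS". Age and BMI are to be categorised. KL grade appears nowhere in the section.
- **Inclusion criteria:** KOA patients must "have X-ray examination showed Kellgren-Lawrence grade" II or higher, on a film no more than 6 months old.
- **Discussion:** the patients are described as "a typical KOA population with any KL grade other than grade I", so grade is not held constant by design.
- **Disease-related data:** the list opens "Disease-related data included NRS [29], pain sites (front, back, outside or inside), duration of pain" and goes on to pain descriptors and pain activities. KL grade is not on it.
- **Introduction:** the authors state that "thermal alteration can reflect the progress of KOA and guide medical practice".

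**The concern.** A more advanced joint may be both more painful and different in skin temperature. If so, disease stage is a common cause of NRS and of the outcome, and a model without it credits part of the stage effect to pain level. The same can happen to pain site if the painful area differs by stage.

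The protocol's own reasoning makes this plausible. Besides the Introduction, the Discussion says that inflammatory change in joint tissue shows in skin temperature. It also treats new vessel growth as a source of pain and its blood-flow effects as visible on thermography. KL grade is the only measure of structural progression that the article mentions, and screening already requires it.

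The stake is interpretation of the secondary objective. Temperature that varies with pain level and temperature that varies with disease stage mean different things for choosing acupoints, and the authors plan a randomised trial of temperature-guided selection after this study.

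**Working it through.** **The plan's own figure.** The article gives no figure for this model. Its only sample-size figure is for the primary comparison: means 0.11 and −0.23 °C (difference 0.34), SD 0.79, two-sided α = 0.0045, power 80%, stated n = 149. The normal approximation gives 147 per group and the noncentral t gives 149 (power 0.802). The figure reproduces, and it has no bearing on this point.

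**Inputs for the check.**
- Patients in the model: 170 KOA patients as recruited, or 170 × 0.85 = 144.5, taken as 145, after the stated 15% attrition. The model is read as covering KOA patients only, because the objective says so and NRS and pain site are disease-related data.
- Significance level: 0.05, the level set for measurements other than acupoint relative temperature. A factor score is read as falling under it.
- r, the correlation of NRS with KL, and b, the standardised effect of KL on the factor score. The documents give neither. Both are assumptions, varied from 0.1 to 0.5, and both are meant as partial values given age, gender, BMI and pain site, which the model already contains.
- The true NRS effect is set to 0.

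**Formulas.** With KL omitted, the apparent standardised NRS slope is ρ = r × b. By Fisher's z, the test statistic is centred at z = atanh(ρ) × √(N − 3), and the chance of P < 0.05 is 1 − Φ(1.96 − z) + Φ(−1.96 − z).

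**Worked case, r = b = 0.3.** ρ = 0.3 × 0.3 = 0.09.
- N = 145: z = atanh(0.09) × √142 ≈ 1.08, chance 18.9%.
- N = 170: z = atanh(0.09) × √167 ≈ 1.17, chance 21.5%.

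**Range along r = b.**

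| r = b | Apparent slope | Chance of P < 0.05, N = 145 | N = 170 |
|---|---|---|---|
| 0.1 | 0.01 | 5.2% | 5.2% |
| 0.2 | 0.04 | 7.6% | 8.1% |
| 0.3 | 0.09 | 18.9% | 21.5% |
| 0.4 | 0.16 | 48.5% | 55.0% |
| 0.5 | 0.25 | 86.1% | 91.0% |

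With KL in a correctly specified model, the expected NRS slope is 0 and the chance returns to 5%.

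**Limits.** The calculation treats NRS as linear and ignores the few degrees of freedom used by the other factors. It covers NRS only; no figure was worked out for pain site, where the argument is qualitative.

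**The case against.** The strongest reply is that this is an exploratory model and nothing in the article contradicts it. Whether temperature differs by pain level can be answered descriptively without KL; a pain effect independent of radiographic stage is a different quantity, which the article does not expressly claim to estimate. This stands in part. If only the total association is wanted, omitting KL is no error. But an objective about influence, and an analysis of contributory factors, read as more than description. Reporting both estimates serves either reading.

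Second, the factor list is not declared closed, and the article condenses a fuller protocol. True, but the article does name the factors, and no visible text adds KL to any analysis.

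Third, the confounding path is only partly documented. The Introduction speaks of disease progress, not of KL grade, and nothing in the article links KL to NRS. Admitting only NRS 4 or higher may weaken that link, and factors already in the model may carry some of the severity. All of this stands, and it is why the range must include the negligible end.

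A reader might also infer more than the documents support:
- **That the needed grade is already on file at no cost.** The entry criterion sets a threshold. It does not say that the individual grade is kept, or which knee it refers to. Bilateral pain is admitted, and the evaluated side is the one with worse symptoms.
- **That the bias can be put in degrees.** Multiplying 0.09 by the SD of 0.79 °C gives 0.07 °C, but that SD belongs to acupoint relative temperature and the outcome here is a factor score.
- **That duration of pain must be added too.** It is collected and not used in the model, but nothing beyond that argues for it, and this point does not need it.

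**Conclusion.** The gap is real and modest in weight. The one model named for the secondary objective omits a severity measure that screening must assess and that varies among patients, so an NRS or pain-site effect cannot be separated from disease stage. This shows that confounding is possible, not that it will occur.

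Its size cannot be settled from the documents. Under the assumed r and b, it lies anywhere between no practical effect and a false NRS finding in most studies; the middle case of about one in five is an illustration, not an estimate. KL is also an imperfect proxy for inflammation, so adjusting for it would reduce such confounding without necessarily removing it.

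A reader might take this as a threat to the study's main result. It is not: the KOA-versus-healthy comparison does not use this model.

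**What to change.** 1. In Disease-related data, list the individual KL grade (II, III or IV) of the evaluated knee, taken from the eligibility X-ray.
2. In Statistical analysis, state that the model is fitted in KOA patients and add KL grade as a categorical factor.
3. Report the NRS and pain-site effects with and without KL grade, and describe the version without it as a total association.

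Cost: one extra recorded field, a check that the grade refers to the knee chosen for evaluation, and two degrees of freedom (three grades less one) among roughly 145 to 170 patients. Where the film on hand does not cover that knee, the grade would be missing, and the number of such patients should be reported.
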